**Fig. 1 Fig1:**
[figure not shown]
Study plan for phase I

**Phase II (follow-up Study)** involves following and comparing behavioral and attitudinal changes towards oral health and oral health-related quality of life among parental groups from different cultural backgrounds (immigrants, previously involved in phase I and native Norwegians), It also includes BMI measurements of children, and caries status in both the test group (immigrant, IM) and the control group (Norwegian, N) over a two-year period. (Fig. 2).

**Fig. 2 Fig2:**
[figure not shown]
Study plan for phase II

### Study population

Parents were recruited from the municipality of Bergen, Norway.

### Inclusion criteria

#### Phase I

Immigrant parents (IM) of infants (0–6 months old) with NW background (Eastern Europe, Asia, Africa, Turkey, South and Central America) were recruited from different primary health care centers in the municipality of Bergen, Norway. Before the recruitment phase, the health centers were allocated to either intervention or control groups.

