### Screening and recruitment process

The health centers selected for participation have different uptake areas within the municipality of Bergen and have high numbers of parents of immigrant background enrolled. Before vaccination, the medical staff of the primary health care centers briefed the parents about the project and those who were interested in learning more about the study were directed to a room where they received further details from the researchers involved in the project. The researchers were responsible for handling requests to participate in the study, information about the study and handing out the consent form. During waiting time and after the child’s vaccination, personal interviews were conducted with those parents who were willing to participate/sign the consent form (Fig. 3).

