**Fig. 3 Fig3:**
[figure not shown]
Consort diagram. This figure illustrates the study design (RCT). A total of 7 health centers having 475 participants with children 0-6 months were randomized to an intervention arm and a control arm. RCT, randomized controlled trial

While parent and child waited for the recommended time before discharge after vaccination, an experienced dental professional researcher explained the purpose of the study and provided participating immigrant parents (IM) with the interview schedule. The intervention group received additional information on oral hygiene, modifying dietary risk behaviors, and dietary guidance, while the control group received the regular health information provided at the primary care centers.

Strategies to promote retention include provision of health information. The family was issued with a toothbrush for the child and a plastic mouth mirror for the parent to check the oral cavity.

The child included in the study was referred for dental treatment if needed (the child’s first routine visit to the dentist is at 3 years of age). Reminders about upcoming interviews were sent to the participants and confirmed by telephone.

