### Randomization

Health centers in the municipality of Bergen (i.e., health centers agreeing to participate in the study) were randomly allocated to intervention or control groups by researchers involved in the study. Instead of randomization of individuals within health centers, cluster randomization of the primary sampling unit (health centers) was deemed necessary to avoid contamination of information from those in the intervention group to those in the control group while sharing the waiting room of the same health centers.

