### Statistical analysis

The data will be analyzed using STATA and SPSS version 24 (SPSS Inc., Chicago, II, USA). Descriptive statistics such as mean and standard deviation for continuous variables and frequency and percentage for categorical variables will be presented. Univariable analysis will be based on cross tabulation and Chi Square statistics. Independent sample t test will be used to assess how sum scores of knowledge, attitudes and the parent’s own oral hygiene and dietary habits varied according to the parents’ age, educational level, and duration of residence in Norway. Differences between intervention and control groups will be analyzed using T-tests and associations will be quantified using eta coefficients. A two-sided significance level of 5% will be applied in all analyses.

Primary analysis will follow an “Intention-to-treat” approach. Comparison between the intervention and control groups at baseline and follow-up to calculate intragroup changes of outcome variables will be performed using generalized linear model (GLM) repeated measures. In the secondary analysis, ‘per-protocol’ approach will be used, where the participants would be excluded if they (1) did not participate in the intervention program, (2) did not complete the questionnaires, (3) were not eligible according to the inclusion and exclusion criteria.

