The main strength of this study is that it is a randomized trial, making it possible to evaluate the effectiveness of an intervention program to prevent caries and obesity. The use of cluster randomization allows the identification of the intervention effects when randomization at individual level is not appropriate. Cluster randomization may help to prevent contamination caused by sharing of information between intervention and control participants. Using a culturally adapted health intervention program, focusing on dietary- and oral hygiene practices among NW immigrant families attending primary health care centers might positively impact parental attitudes towards the oral health of their children. In this study, the collaboration between dental public health and primary health care personnel using the CRFA and MI is an innovation which offers opportunities to address key dietary behaviors that may improve general and oral health, particularly among at-risk children.

A possible limitation of this study is that data will be collected by means of a self-reported questionnaire, in which participants might be inclined to give more socially acceptable answers. The diverse backgrounds and different periods of residence in Norway might influence comparisons between groups as well as the acculturation effects. Finally, the two sessions for data collection limit the potential to draw causal inferences about the influence of parental characteristics on their hygiene/feeding practice knowledge and attitudes.

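### Centres were allocated before recruitment and only six or seven were randomised, yet neither planned between-arm analysis includes baseline covariates or centre

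*Protocol article*

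**What the plan says.** **Allocation and recruitment.** Inclusion criteria, Phase I: "Before the recruitment phase, the health centers were allocated to either intervention or control groups". Under Randomization, the centres "were randomly allocated to intervention or control groups by researchers involved in the study". No stratification or matching of centres is described there. Under Screening and recruitment process, centre medical staff brief parents first, and then: "The researchers were responsible for handling requests to participate in the study, information about the study and handing out the consent form". The text after Fig. 3 adds that "an experienced dental professional researcher explained the purpose of the study and provided participating immigrant parents (IM) with the interview schedule". The same section says the centres have different uptake areas.

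**Number of centres.** The Sample size section works with six centres, three per arm. The Fig. 3 caption gives seven centres and 475 participants.

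**Analysis.** Statistical analysis states: "Differences between intervention and control groups will be analyzed using T-tests and associations will be quantified using eta coefficients". Its next paragraph, which opens with the intention-to-treat primary analysis, says the comparison of the arms at baseline and follow-up "will be performed using generalized linear model (GLM) repeated measures". Neither sentence names a covariate or a centre term. Parents' age, education and length of residence appear in that section only as factors against which sum scores are compared by t-test.

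**Available data.** Data collection instrument lists parental education, occupation and years of residence in Norway. Knowledge and behaviour are measured at 0–6 months and, as the knowledge outcome specifies, again at 18–24 months. Caries at 24 months has no baseline, because no teeth have erupted at 6 months.

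**Acknowledged limitation.** In the Discussion: "The diverse backgrounds and different periods of residence in Norway might influence comparisons between groups as well as the acculturation effects".

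**The concern.** When centres are allocated first and parents are asked to join afterwards, randomisation settles which centres are in which arm but not which parents enter. Study researchers knew the allocation, and researchers ran the information and consent step, so uptake could differ by arm. Separately, three or four centres per arm with different catchments will seldom be well balanced on parents' background, even with perfect recruitment.

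The article recognises that background and residence could affect group comparisons, and it collects the relevant variables. Yet the arm comparisons it fixes use neither those variables nor the randomised unit. An intention-to-treat set does not help, because it protects against exclusions after entry and not against differences in who enters. At stake are the size of the estimated effect and the credibility of its p-value, in a trial whose Discussion presents randomisation as the main strength.

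**Working it through.** **Inputs from the Sample size section:** six centres, three per arm; about 50 parent/child pairs per centre, 300 in total (150 per arm); centre SD 0.1 or 0.25; effect 0.25. **Assumptions:** residual SD 1, and the 0.25 effect on the same scale as the centre SDs. The section does not state either.

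**1. The plan's own figure.** The total of 300 can be neither confirmed nor refuted, because target power and residual SD are not given and Fig. 4 is not shown. With residual SD 1 and no clustering, 150 per arm gives 58% power at 0.25. This point does not depend on that figure.

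**2. Chance imbalance from centres.** SD of the arm difference = centre SD × √(1/3 + 1/3).
- Centre SD 0.1: 0.1 × 0.816 = 0.082.
- Centre SD 0.25: 0.25 × 0.816 = 0.204.
- With seven centres split 3 and 4, the factor is √(1/3 + 1/4) = 0.764, giving 0.076 and 0.191.

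With three per arm, the probability that centre effects alone produce a difference of 0.25 or more in either direction is 2 × (1 − Φ(0.25/SD)): 0.2% at centre SD 0.1 and 22% at centre SD 0.25.

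These figures describe centre variation in whatever outcome is compared. The article gives no separate centre SD for change scores, which could be smaller.

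**3. Error rate of a t-test that ignores centres.** ICC = SD²/(1 + SD²); design effect = 1 + 49 × ICC; type I error ≈ 2 × (1 − Φ(1.96/√design effect)).

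| Centre SD | ICC | Design effect | Type I error (formula) | Type I error (20,000 simulations) |
|---|---|---|---|---|
| 0.1 | 0.010 | 1.49 | 10.8% | 10.6% |
| 0.25 | 0.059 | 3.88 | 32.0% | 32.6% |

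The nominal level is 5%.

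**4. Imbalance in the baseline score.** Let the arms differ by b at baseline, with baseline/follow-up correlation ρ. Assume b = 0.2 SD and ρ = 0.3 to 0.7; the article gives neither.
- If the imbalance lies only in the measured baseline score, a follow-up t-test is biased by ρb = 0.06 to 0.14 SD. A change comparison is biased by (ρ − 1)b = −0.14 to −0.06 SD. A baseline-adjusted comparison is biased by 0.
- If the imbalance is a stable difference between the parents in the two arms, a follow-up t-test carries the full 0.2 and the change comparison carries 0. Adjustment for baseline score alone leaves (1 − ρ)b = 0.06 to 0.14 SD. This is why education and residence belong in the model too, and why adjustment cannot be presented as a complete cure.

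**5. Caries at 24 months.** There is no baseline to subtract or adjust for. Any difference between the arms' parents that is related to caries passes into the comparison, and only covariates such as education and residence can reduce it.

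**The case against.** **The GLM.** A reader who stops at the t-test sentence might infer that imbalance goes straight into the primary effect estimate. The article does not support that. The repeated-measures GLM stands in the primary-analysis paragraph, both primary outcomes are changes from a 0–6 month baseline, and an arm-by-time comparison removes stable level differences. This objection stands for knowledge and behaviour. It does not help with regression to the mean, differential change or clustering, and it does not reach follow-up-only comparisons.

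**Who did what.** A reader might infer that the same individuals allocated, consented and interviewed. The article refers to researchers at each step but never says they are the same people, and the sentence on interviews is passive. It reports no difference in uptake between arms. Recruitment bias is therefore a threat created by the design, not a demonstrated fact.

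**Size.** It is tempting to quote a bias of about 30% of the planning effect. If centres differ in the share of low-education parents with SD 10 points, a 2-SD imbalance over 3 and 4 centres is 2 × 0.10 × 0.764 = 0.153. At 0.5 SD per unit that is 0.076 SD, and 0.076/0.25 = 31%. Both inputs are assumed and the imbalance is an extreme. It is also chance variation with mean zero, which a random centre effect would carry into the standard error. It does not measure recruitment bias, and a stable education effect on level drops out of a change comparison.

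**Left to the analysis plan.** An article need not list its adjustment set, and allocating centres first is common where participants present over time. Both are fair. However, this article does fix its between-arm methods, and as fixed they take no account of the randomised unit or of influences it acknowledges.

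**Conclusion.** The point holds in limited form. Allocation before recruitment, researchers in both the allocation and consent steps, and six or seven centres with different catchments leave the arms open to recruitment differences and chance imbalance. Neither stated analysis includes a baseline covariate or centre. The consequence is direct for follow-up-only comparisons, above all caries at 24 months. For knowledge and behaviour it is partial, provided the GLM is read as an arm-by-time comparison.

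On the plan's own centre SDs, with residual SD 1 and three centres per arm, centre effects alone give an arm difference with SD 0.08 to 0.20 against a planning effect of 0.25. At the upper value the t-test's error rate is about 32%. These figures measure chance variation and clustering. The size of any recruitment bias cannot be derived from the article. The change is worth making because the needed variables are already collected.

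**What to change.** Make the primary between-arm analysis a model of the follow-up score on arm, adjusted for baseline score, parental education and years of residence in Norway, with centre as a random effect and a small-sample correction for the six or seven centres. Use the same covariates and centre term, without a baseline score, for caries at 24 months. Report the unadjusted result as secondary. State in the limitations that adjustment cannot remove unmeasured recruitment differences.

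The change is one of analysis wording and needs no new data. Adjustment uses a few individual-level degrees of freedom. Intervals will be wider. With residual SD 1 and no covariates, the standard error rises from √(2/150) = 0.115 to √(2 × (0.1²/3 + 1/150)) = 0.141 at centre SD 0.1, or √(2 × (0.25²/3 + 1/150)) = 0.235 at centre SD 0.25. With a t reference on 4 degrees of freedom, power at 0.25 is then 28% or 13%, against 58% when centres are ignored. Baseline adjustment should recover some of this. The rest reflects uncertainty that the stated methods do not show.

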#### Phase II

The immigrant parents involved in the intervention study (IM) and a new group of parents of Norwegian background (N) will be recruited from similar public dental health clinics when they visit these centers for their children’s routine oral health examinations at the ages of 3 and 5 years.

### Exclusion criteria

Parents who were unwilling to participate or whose babies had serious congenital defects, requiring frequent oral health checks, were excluded.

### Screening and recruitment process

The health centers selected for participation have different uptake areas within the municipality of Bergen and have high numbers of parents of immigrant background enrolled. Before vaccination, the medical staff of the primary health care centers briefed the parents about the project and those who were interested in learning more about the study were directed to a room where they received further details from the researchers involved in the project. The researchers were responsible for handling requests to participate in the study, information about the study and handing out the consent form. During waiting time and after the child’s vaccination, personal interviews were conducted with those parents who were willing to participate/sign the consent form (Fig. 3).

**Fig. 3 Fig3:**
[figure not shown]
Consort diagram. This figure illustrates the study design (RCT). A total of 7 health centers having 475 participants with children 0-6 months were randomized to an intervention arm and a control arm. RCT, randomized controlled trial

While parent and child waited for the recommended time before discharge after vaccination, an experienced dental professional researcher explained the purpose of the study and provided participating immigrant parents (IM) with the interview schedule. The intervention group received additional information on oral hygiene, modifying dietary risk behaviors, and dietary guidance, while the control group received the regular health information provided at the primary care centers.

Strategies to promote retention include provision of health information. The family was issued with a toothbrush for the child and a plastic mouth mirror for the parent to check the oral cavity.

The child included in the study was referred for dental treatment if needed (the child’s first routine visit to the dentist is at 3 years of age). Reminders about upcoming interviews were sent to the participants and confirmed by telephone.

### Sample size

Statistical power (+/- 95% CI) to detect a fixed effect the size of 0.15 or 0.25 (left and right panels, respectively) and with a random effect of clusters (health stations), measured in standard deviations, was set to 0.1 or 0.25 (top and bottom panels, respectively). Power was calculated over a range of sample sizes using the power Curve function from the *simr* R library. The number of clusters (health stations) is six, i.e., three per treatment group. Each data point and associated confidence interval are estimated from 1000 Monte Carlo simulations. The results indicate that a total sample size of at least 300 participants (approximately 50 parents/child pairs from each center) is needed to ensure adequate power, given that the effect size is no smaller than 0.25 (Fig. 4).

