## Methodology

### Trial Design

This is a cluster randomized controlled intervention follow-up study. By integrating primary health care and the public dental health service, the basis of the study is the application of an early-life intervention program among parents/children of immigrant backgrounds, using the MI technique and CRFA to prevent dental caries and obesity, thereby improving their general health, oral health, and quality of life. Primary care health centers in the municipality of Bergen, Norway, were randomly allocated to intervention or control groups (allocation ratio 1:1), to evaluate the efficacy of the culturally adapted dietary/hygiene advice. The intervention group received guidance on diet/hygiene and the control group received standard care, including regular health information at the primary care health centers. The study has been funded by the Norwegian Research Council for three years.

The study has two phases:

**Phase I (The Intervention Study)** involves assessing oral health-related knowledge, attitudes, and behavior among immigrant parents of infants (0–6 months). It also involves investigating the potential of a culturally adapted oral health education intervention to prevent the development of ECC and to improve parental oral health-related knowledge and awareness (Fig. 1).

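### The stated inputs (0.25 SD effect, 300 parents, six centres) give about 13–42% power, not adequate power, and the six-centre basis conflicts with the seven centres randomised

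*Protocol article*

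**What the plan says.** The Sample size section describes a simulation of power "to detect a fixed effect the size of 0.15 or 0.25", with a random effect for health station that, "measured in standard deviations, was set to 0.1 or 0.25". On clusters it says: "The number of clusters (health stations) is six, i.e., three per treatment group". It concludes that "a total sample size of at least 300 participants (approximately 50 parents/child pairs from each center) is needed to ensure adequate power", subject to one condition: "given that the effect size is no smaller than 0.25". The conclusion is not restricted to the smaller cluster SD. The text gives no numerical power target and no residual SD. Fig. 4, which holds the power curves, is not reproduced in the text available to me.

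The Statistical analysis section adds: "A two-sided significance level of 5% will be applied in all analyses".

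Two other places describe the design differently. The Fig. 3 caption says: "A total of 7 health centers having 475 participants with children 0-6 months were randomized". The Trial Design section says that the centres "were randomly allocated to intervention or control groups (allocation ratio 1:1").

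**The concern.** An effect of 0.25 SD is small, and 150 per arm falls short of the usual 80% even for individually randomised parents. Here the centre is the randomised unit and there are only three per arm, so between-centre variation sets a floor under the standard error that recruiting more parents cannot lower. A statement that 300 parents suffice therefore looked wrong on its face, most clearly at the larger of the two cluster SDs that the section itself simulates.

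At stake is how the primary result will be read. A non-significant difference from a trial declared adequately powered for 0.25 would be taken as evidence that the intervention does not work, when the design would probably miss an effect of that size. The number of centres matters too: it fixes the degrees of freedom for a centre-level comparison (4 with six centres, 5 with seven), and the article gives two different numbers.

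**Working it through.** **Inputs**

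- Effect d = 0.25; cluster SD s = 0.1 or 0.25; six centres (3 + 3); 50 parents per centre, so 150 per arm (Sample size).
- Two-sided 5% (Statistical analysis).
- Seven centres and 475 participants (Fig. 3 caption).
- Assumed because not stated: individual (residual) SD 1, a single follow-up score, 80% as the benchmark for adequate power, and for seven centres a 3/4 split with equal centre sizes (475/7 ≈ 68).

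The plan's own power value cannot be reproduced, because the text prints none.

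**Step 1: no clustering**

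SE = √(2/150) = 0.1155, and 0.25/0.1155 = 2.165. Power is 58%. For 80% power, n per arm = 2 × (1.96 + 0.84)² / 0.25² = 2 × 7.849 / 0.0625 = 251.2, so 252 against the 150 planned. The claim already fails here.

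**Step 2: with the stated clustering**

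SE = √[ s²(1/k₁ + 1/k₂) + (1/n₁ + 1/n₂) ], with k centres and n parents in each arm.

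- Six centres, s = 0.1: √(0.01 × 2/3 + 2/150) = √0.0200 = 0.141; ratio 1.77.
- Six centres, s = 0.25: √(0.0625 × 2/3 + 2/150) = √0.0550 = 0.235; ratio 1.07.
- Seven centres, 475 parents: SE 0.120 and 0.212; ratios 2.08 and 1.18.

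| Design | Cluster SD | Power, normal | Power, t | Effect detectable at 80% (t) |
|---|---|---|---|---|
| 6 × 50 | 0.1 | 42% | 28% (4 df) | 0.53 SD |
| 6 × 50 | 0.25 | 19% | 13% (4 df) | 0.88 SD |
| 7 centres, 475 | 0.1 | 55% | 39% (5 df) | 0.42 SD |
| 7 centres, 475 | 0.25 | 22% | 16% (5 df) | 0.75 SD |

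A simulated t-test on centre means for 6 × 50 gave 27% and 13%, in agreement.

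**Step 3: ceiling with unlimited parents**

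With six centres the SE cannot fall below s√(2/3). At s = 0.25 that is 0.204, so power for 0.25 cannot exceed 23% (normal) or 16% (t), whatever the residual SD or recruitment. At s = 0.1 the ceiling is 86% or 64%.

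**Step 4: readings that might rescue the claim (6 × 50)**

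- *Baseline adjustment*, multiplying the individual variance by (1 − r²): with r = 0.8, power is 65% (normal) or 43% (t) at s = 0.1, and 21% or 15% at s = 0.25.
- *The 0.25 as a ±1-coded coefficient*, a true difference of 0.5 SD: 94% or 75% at s = 0.1, but 57% or 37% at s = 0.25.
- *Smaller residual SD*: 80% at s = 0.1 needs a residual SD of about 0.3 and a normal test. At s = 0.25 the ceiling in Step 3 applies.
- *Mixed-model tests by simulation* (REML Wald z; likelihood ratio): 42% and 43% at s = 0.1, 26% and 27% at s = 0.25. Under no effect these tests reject in 7% of trials at s = 0.1 and 11–12% at s = 0.25, so part of that power is excess type I error.

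**Step 5: number of centres**

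The Sample size section states six centres, three per group. The Fig. 3 caption states seven randomised. The Trial Design section states 1:1 allocation of centres, which seven units cannot satisfy. Nothing in the article connects the three.

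**The case against.** The strongest reply is that the article does not state the model used here. It gives no residual SD, test or power target, and the phrase about standard deviations attaches grammatically to the cluster effect rather than to the 0.25. The primary outcome is a change from 0–6 to 18–24 months, analysed by repeated measures. In a group-by-time contrast whose only random effect is a centre intercept, the centre term cancels. Then SE = √(2(1 − r) × 2/150), and normal-test power for 0.25 is 58% at a baseline–follow-up correlation r of 0.5, 80% at 0.7 and 93% at 0.8.

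This does not save the statement. It needs an unstated correlation of at least 0.7, a normal reference distribution (with t on 4 df the last two figures drop to 56% and 73%) and no centre-by-time variation. It also does not fit the section's own description: if the centre effect cancelled, simulating cluster SDs of 0.1 and 0.25 in separate panels would give identical results.

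It can also be said that no 4-df test is specified, so the 13% and 28% rest on a choice of test. That is true, and it is why the normal-test figures stand beside them; those fall short as well.

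Finally, six may be the planned and seven the actual number of centres, and 3/4 is as close to 1:1 as seven allows. That is plausible, and this part is secondary. But the article states six as a present fact and does not explain the change.

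What stands of the objection: the exact percentages depend on the assumed residual SD, and the authors' simulated values cannot be compared without Fig. 4.

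**Conclusion.** The concern holds. Read as printed, the inputs give between 13% (cluster SD 0.25, t on 4 df) and 42% (cluster SD 0.1, normal test) power for 0.25 with 300 parents in six centres. The seven centres and 475 participants reported as randomised raise this only to between 16% and 55%. These figures assume an individual SD of 1 and a single follow-up score.

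The failure at cluster SD 0.25 is firmer. For a between-centre comparison it holds at any residual SD and any number of parents, yet the section makes its adequacy claim conditional on effect size alone. Of the readings tried, only ones the text does not state reach 80%, and none that keeps the centre effect in the comparison does so at cluster SD 0.25.

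The mismatch between six and seven centres is real and unreconciled, but smaller in consequence. The statement of adequate power should not remain as written.

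**What to change.** Rewrite the Sample size section for the trial as run:

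- State seven centres, the actual split between arms and about 68 parents per centre. If six was the planning figure, say so.
- Say what the 0.25 is measured in (outcome SDs or model coefficient, and its coding), and give the residual SD, the outcome (follow-up score or change) and the numerical power target.
- Re-run the simulation with the small-sample cluster test that will be used for the primary comparison, and report power and the detectable effect at both cluster SDs.
- Remove the claim of adequate power for 0.25 unless the re-run supports it at both cluster SDs.
- Bring the Trial Design section, the Fig. 3 caption and the Sample size section into agreement on the number of centres and the allocation.

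The cost is one re-run of an existing simulation and a reworded paragraph. No further participants are required. The stated power will be less favourable, and a null result will have to be interpreted through its confidence interval rather than as evidence of no effect.
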